## What is the proposed duration of treatment?

The treatment period begins following randomization. It consists of day 0 on which baseline measurements will be taken and recorded, and a 14-day treatment period during which domperidone (10 mg × 3/daily) or placebo (3/daily) is administered.

## What is the proposed frequency and duration of follow-up?

Breast milk samples will be obtained on day 0, 4, 7, and 14. Serum prolactin levels will be collected on days 0, 4, and 14. Infant weights will be measured daily. Each participant will be asked questions regarding breast-feeding two weeks following discontinuation of the treatment and at discharge.

## What are the proposed outcome measures?

### a. Primary outcome

The protein levels from breast milk, collected on days 0, 4, 7, and 14 will be compared, between the two groups (taking into consideration the expected rate of decline associated with increasing postpartum days).

### b. Secondary outcomes

The fat, carbohydrate, lactose, energy, calcium, phosphorus and sodium content of breast milk, collected on days 0, 4, 7, and 14, will be compared between domperidone and placebo groups.

### c. Other outcomes

Daily breast milk volumes (if the infant breast feeds, volume will be estimated using pre and post feeding weights), serum prolactin levels, daily infant weights, and breastfeeding rates two weeks after treatment completion and at discharge.

## Sample size

Sample size was calculated using a 2-sided test, an alpha error of 0.05 and a power of 80 percent. Based on the medical literature and prior clinical understanding, we designed the study to detect as significant a 20 percent or greater change in protein content (in the domperidone group relative to the placebo group). We will also have sufficient power to detect a 20 percent or greater change in fat content and a 10 percent or greater change in energy content, if such differences are in fact caused by domperidone. Means and standard deviation values for protein, fat and energy content used in the sample size calculation were obtained from a recent, authoritative publication on the breast milk content of preterm human milk [74]. Based on this calculation our study will recruit 44 participants, 22 assigned to the domperidone group and 22 to the placebo group.

## What is the planned recruitment rate?

In the year 2000, 58 surviving infants less than 31 weeks gestation were admitted to the Neonatal Intensive Care Unit. Of these 20–25 percent were multiple births. Breastfeeding initiation rates are 80–85 percent in our nursery. Due to the lack of information regarding the incidence of lactation failure in this population, a convenience (2001) survey of mothers of preterm infants providing breast milk for their babies was carried out. Fifty-five percent of these mothers had experienced lactation failure, several of whom had been prescribed domperidone (domperidone is not prescribed routinely in this centre). Therefore, 20–23 women a year will be eligible for the study. Recruitment rates for research studies in our NICU range from 60–100 percent. Based on previous studies done in this setting where risk is minimal and side effects are rare, we estimate a greater than 90 percent recruitment rate.

## Will compliance be a concern?

Since side effects are rare, we do not anticipate problems with compliance. The majority of mothers will be visiting their baby on a regular basis, hence providing milk and blood samples should not be a great inconvenience. Participants will receive their 2-week supply of domperidone or placebo following enrollment. They will be provided with instruction related to self-administration and asked to return the medication vial and any unused medication at the completion of the two-week period. Pill counts will be done in pharmacy to ensure drug accountability and evaluate compliance. The study nurse/investigators will be in close contact with the mothers and review instruction related to medication on study days 4, 7 and 14.

Based on our past clinical observations, we anticipate that the majority of the participants enrolled will be mothers of infants delivered between 24–28 weeks gestational age. The infants will be 29–33 weeks corrected gestational age at the end of the study period. Although many of these infants will receive skin to skin care from their mothers (kangaroo care), few will be actively breast feeding. For those infants who are enrolled at a later gestational age (who will be closer to 35 weeks at the end of the study period) and able to begin breast-feeding, milk volumes will be calculated using pre and post feeding weights. Mothers will be asked to refrain from breast-feeding and to express breast milk on days 0, 4, 7 and 14 as per our usual practice to ensure that a 24-hour pooled breast milk sample will be obtained. Recruitment and compliance therefore will not be adversely affected.

## What is the likely rate of loss to follow Up?

The Neonatal Intensive Care Unit (NICU) is the tertiary level neonatal unit for all of Nova Scotia and for most of the Maritime Provinces. Most babies in the NICU stay until discharged from hospital. Approximately 20 percent return to local hospitals prior to discharge home. However, very few are transferred prior to 35 weeks corrected gestational age. Mothers of any infants transferred prior to discharge will be provided with a toll free telephone number and instructed to notify the principal investigator or study nurse of their discharge home. Answers to follow-up questions will be obtained by telephone by either the principal investigator or study nurse. In addition, most infants that meet inclusion criteria for this study (all Nova Scotia and Prince Edward Island babies born at less than 31 weeks) continue to be followed until three years of age as part of the IWK Perinatal Follow-up Program. This program loses two to three percent to follow-up. We therefore do not expect any significant losses to follow up.

## What is the proposed type and frequency of analysis?

### a. Method of breast milk collection

Throughout the study, breast milk will be expressed according to the standard practice of the nursery. Breast milk will collected using the Symphony reusable breast pump (Medela Canada). Each participant will be supplied with a double pump collecting system and sterile collection bottles. Each woman will be instructed to collect 24-hour samples of breast milk for the day prior to beginning treatment and then each day for the two-week period. A new container will be used for each pumping. Each participant will keep a diary to record the amount of milk pumped, the date and time as well as ensure that adhesive labels with this information also be placed on each of the containers. Daily milk volumes will be calculated. On days 0, 4, 7 and 14, two small samples (1 ml and 30 mls) of milk (from a pooled 24 hour collection) will be retained for analysis. The remainder of the milk will be available for the infant as usual.

### b. Chemical analysis

Breast milk samples (24 h – pooled) will be frozen (-70 C) and couriered in batches of eight for analysis of macronutrient content to the Prince Edward Island Food Technology Centre. Total nitrogen will be determined using the Kjeldahl method [75]; fat by the Roese-Gottlib method; ash and moisture by Forced Air Oven: and, energy, carbohydrate and lactose concentrations will be calculated [78].

Mineral content will be analyzed at the IWK Laboratory Department. Samples will be centrifuged and the aqueous component assayed [79]. Phosphorous content will be measured using the Ammonium molybdate method on the Ortho Vitros^®^) chemistry analyzer [80]. Calcium content will be determined using the Arseno (III) method on the Ortho Vitros^®^) chemistry analyzer [81]. Sodium content will be determined by ion selective electrode [82].

Mothers will also be asked to provide blood samples to determine prolactin concentrations prior to the initial dose, on day four and day 14. Serum prolactin levels will be collected at the IWK Health Centre outpatient tab and measured using Chemiluminescence immunoassay on the Vitros^®^) Eci analyzer [83]. Each participant will receive, requisitions for blood collection dated for the appropriate study days required. If a participant is unable to come to the IWK Health Centre, the principle investigator or study nurse will make alternate arrangements with her family doctor and local laboratory to ensure that the specimen is collected.

### c. Statistical analysis

Analysis and inference will be based on the intention-to-treat principle. Efforts will be made to ensure that follow up is complete for all subjects and that there are no missing values for any of the subjects for any variable. Blinding of group assignment will be retained until after the analysis is completed. Baseline characteristics of study subjects will be contrasted to ascertain that randomization has in fact produced comparable groups with respect to all variables that effect the composition of breast milk including gestational age at delivery and duration since delivery. The primary outcome of interest will be a potential decline in breast milk protein content over time within the domperidone group versus the placebo group. This analysis will compare the means in the two groups before and after treatment and contrast the mean difference between groups using 95 percent confidence intervals and a p value. The stratified nature of the randomization will be accounted for in the analysis. If differences are noted in baseline characteristics, inferences will be made based on observed and (linear regression) adjusted differences between groups. Analysis for fat, lactose, energy, calcium, phosphorus and sodium content in expressed breast milk will be done in an identical fashion as for protein by comparing the means in the two groups before and after treatment and contrasting the mean differences between groups using 95 percent confidence intervals and a p value. Prolactin levels will be compared between the two groups and used to determine the correlation between prolactin levels and volume of milk produced.

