### h. Breast milk composition

Human breast milk composition is widely variable both within and between breast-feeding mothers [63]. Variation in macronutrient composition can occur at various feeding times throughout the day or night and also at the beginning and end of a feed [64]. These variations have been reported to be greater in mothers of preterm infants providing expressed breast milk. Measuring samples taken from pooled 24-hour collections may limit the degree of variability reported. Variation in the composition of human breast milk has been associated with the diagnosis of either sporadic or chronic mastitis. The sodium content of the breast milk is the constituent most profoundly affected [66].

The composition of preterm mother's milk also differs from that of term mother's milk [67-69]. Although protein levels are initially higher in preterm breast milk, the natural temporal decline of protein content creates a nutritional deficit when compared to the needs of the preterm infant [5]. Studies show that there is a decline in protein content following delivery, while fat, lactose and energy content increases. These trends are more pronounced during the first 3 weeks and are greatest in the preterm group [64]. In a more recent study, random spot samples of breast milk from mothers of premature infants were analyzed to estimate macronutrient variability. Although fat content was highly variable within and between individuals, it remained fairly constant throughout lactation. Protein was less variable but was found to decrease significantly throughout the first four weeks of lactation (r = -0.45, p < 0.001), then continued to fall at a slower rate of decline over time and with increased volumes of breast milk [70]. Several studies have reported similar findings [67,70-74].

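### The primary contrast of before-after changes is not matched to the content SDs used for sizing; a prespecified day-0-adjusted ANCOVA would close the gap at almost no cost

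*Protocol article*

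**What the plan says.** **Analysis.** The Statistical analysis section of the protocol article describes the primary protein comparison as follows: "This analysis will compare the means in the two groups before and after treatment and contrast the mean difference between groups", with a 95% confidence interval and a p value. Fat, lactose, energy, calcium, phosphorus and sodium are to be handled in the same way. Stratification is to be accounted for. Covariate adjustment depends on what is seen: "If differences are noted in baseline characteristics, inferences will be made based on observed and (linear regression) adjusted differences between groups". The baseline variables named there are gestational age at delivery and time since delivery; day-0 milk concentration is not among them. Milk is sampled on days 0, 4, 7 and 14, and the section does not say which day, or which summary of days, counts as after treatment.

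**Sizing.** The Sample size section states: "Sample size was calculated using a 2-sided test, an alpha error of 0.05 and a power of 80 percent". The target is a "20 percent or greater change in protein content (in the domperidone group relative to the placebo group"). The same number is said to be enough for a "20 percent or greater change in fat content and a 10 percent or greater change in energy content". On the inputs it says: "Means and standard deviation values for protein, fat and energy content used in the sample size calculation were obtained from a recent, authoritative publication". The result is that "our study will recruit 44 participants, 22 assigned to the domperidone group and 22 to the placebo group". No mean, SD, SD of change or correlation is given.

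**The concern.** The SD of a content value and the SD of a within-woman change are different quantities, and the ratio between them depends on rho. If the trial was sized on the first and is analysed on the second, the stated 80% does not automatically belong to the stated analysis.

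A change contrast also subtracts the whole of any chance day-0 difference between arms, although only a fraction rho of it is expected to persist. With 22 women per arm, such differences will often be noticeable. The planned remedy is triggered by the data and leaves two answers, observed and adjusted, with neither named as primary.

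At stake are the precision of the main result and a clear single primary estimate, in a centre that expects only 20 to 23 eligible women a year.

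**Working it through.** **Inputs from the Sample size section:** two-sided alpha 0.05, power 80%, 22 per arm, target change 20% for protein and fat and 10% for energy. **Assumed, because not given:** rho from 0 to 0.9, equal SDs before and after, and one post-treatment value unless stated otherwise.

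**1. The plan's own figure.** The total of 44 cannot be reproduced, because no mean or SD is printed. Solving backwards, the standardised difference detectable with 22 per arm is

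d = (1.960 + 0.842) × √(2/22) = 0.845 (normal approximation), or 0.865 (t test).

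A 20% change then corresponds to a coefficient of variation (CV) of 0.20/0.845 = 23.7% (t: 23.1%). For energy, 0.10/0.845 = 11.8% (t: 11.6%).

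**2. Variance relative to a single-time variance of 1.** Post-treatment value alone: 1. Change score: 2(1 − rho). ANCOVA on day 0: 1 − rho².

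Setting 2(1 − rho) = 1 gives a break-even of rho = 0.50, under both the normal and the t calculation.

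**3. Power at 22 per arm, and number per arm for 80%,** taking 22 per arm as exactly 80% on the single-time SD (normal approximation):

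| rho | Change: power | Change: n per arm | ANCOVA: power | ANCOVA: n per arm |
|---|---|---|---|---|
| 0 | 50.8% | 44 | 80.0% | 22 |
| 0.2 | 60.1% | 36 | 81.6% | 22 |
| 0.3 | 65.8% | 31 | 83.6% | 21 |
| 0.4 | 72.5% | 27 | 86.4% | 19 |
| 0.5 | 80.0% | 22 | 89.9% | 17 |
| 0.6 | 87.9% | 18 | 93.8% | 15 |
| 0.7 | 95.1% | 14 | 97.5% | 12 |

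Example at rho 0.3: the change SD is √1.4 = 1.183, so the standardised difference is 0.845/1.183 = 0.714, and power is Φ(0.714 × √11 − 1.960) = Φ(0.41) ≈ 66%.

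Simulation of 20,000 trials at each of four values of rho agrees. ANCOVA gave 78.8%, 82.8%, 89.2% and 97.1% at rho 0, 0.3, 0.5 and 0.7. The loss of about one point at rho 0 is the small-sample cost of estimating the slope.

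**4. How far the 0.5 moves.**
- *Slack in protein.* One sample size serves three outcomes, so protein may not have set it. The break-even is 1 − (0.2368/CV)²/2. It is 0.14 at a protein CV of 18%, 0.30 at 20%, 0.42 at 22% and 0.50 at 23.7%.
- *Averaging days 4, 7 and 14.* With equal correlations, the change variance is (1 + 2rho)/3 + 1 − 2rho = (4/3)(1 − rho). This equals 1 at rho = 0.25.

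**5. Chance baseline imbalance.** The standard error of the day-0 difference is √(2/22) = 0.30 SD. Given an imbalance of that size, the change estimate shifts by (1 − rho) × 0.30 SD. At rho 0.5 this is 0.15 SD, and 0.15/0.865 = 17% of the target effect. The ANCOVA estimate has no such expected shift.

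**The case against.** Several stronger readings are tempting, and the documents do not carry them.

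- *The trial is underpowered.* A reader might infer this from the lower rows of power. No rho, mean or SD is given, and at rho above 0.5 the change contrast does better than the stated 80%.
- *0.5 is a fixed requirement.* It holds only under the conditions in steps 1 to 3. Step 4 shows how readily it falls.
- *The background shows that rho is low.* The Breast milk composition section does say: "Although fat content was highly variable within and between individuals". But that describes random spot samples, whereas this trial assays 24-hour pools, which the same section says may limit variability. It also calls protein, the primary outcome, less variable. Variation between women raises rho, so a remark about variation both within and between women does not settle its size.
- *ANCOVA makes rho irrelevant.* It removes the break-even, but its power still rises with rho.
- *The change contrast is biased.* Over repeated randomisation it is unbiased, and its confidence interval already allows for chance imbalance. The shift in step 5 is conditional on an observed imbalance.

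The plan can also be defended directly. It already provides for regression adjustment and for the strata. That the SDs are single-time SDs is an inference from the wording, and the cited source had repeated samples (282 from 70 mothers). A condensed article may leave the exact model to a fuller plan.

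These points limit the claim but do not remove it. The article does fix the form of the contrast, and it makes adjustment conditional on the data. It names neither day-0 concentration as a covariate nor one of the two resulting estimates as primary.

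**Conclusion.** The point holds as an avoidable weakness in the analysis choice. On its natural reading, the primary contrast uses a variance that the sizing does not describe, and nothing printed links the two.

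If 22 per arm gives exactly 80% on a single-time SD, with equal SDs and one post-treatment value, the change contrast needs rho of about 0.5. It would have about 60% power at 0.2 and 95% at 0.7. Under the same assumptions, a day-0-adjusted ANCOVA keeps about 80% or more across the range and is never materially less efficient. At rho 0.3 the two need 21 and 31 women per arm for 80%.

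Whether any power is actually lost cannot be told from the document. The recommendation does not depend on that, because the adjusted model is the safer choice whichever value of rho applies.

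**What to change.** **Statistical analysis.** Make the primary analysis a prespecified ANCOVA of post-treatment protein on treatment, day-0 protein and randomisation stratum. State whether the response is one named day or a named summary of days 4, 7 and 14. Let this replace both the unadjusted change contrast and the adjustment triggered by observed baseline differences. Use the same model for fat, lactose, energy, calcium, phosphorus and sodium, each with its own day-0 value.

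**Sample size.** State that the 80% was computed from single-time SDs, if that is so, and that it is approximately a lower bound for the baseline-adjusted comparison. If an SD of change was used instead, give it with the assumed correlation.

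**Cost.** A change of wording and one degree of freedom for the day-0 covariate. The day-0 samples are already collected, and the strata must already be accounted for.

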### Randomization

Eligible and consenting woman will be randomized in blocks of four. Pharmacy staff will randomly (using a computer based code) assign mothers to receive either domperidone, 10 mg orally three times daily [17,38] or placebo for a two week period. Mothers of infants >3 but < 4 weeks postpartum will be randomized separately from those ≥ 4 weeks postpartum in order to ensure identical proportions within the domperidone and placebo groups (i.e. randomizations will be stratified by postpartum duration at study entry). Participants will receive their 2- week drug or placebo supply following enrollment. They will be provided with instruction related to self-administration and asked to return the medication vial and any unused medication at the completion of the two-week period. The study nurse/investigators will be in close contact with the mothers and review instruction related to medication on study days 4, 7, and 14.

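### Regression adjustment is triggered by baseline differences, and inference then rests on both the observed and the adjusted result with neither named primary, so the protein outcome can have two conflicting answers

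*Protocol article*

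**What the plan says.** All references are to the Protocol article.

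- **Primary outcome:** breast milk protein on days 0, 4, 7 and 14 is compared between arms, "taking into consideration the expected rate of decline associated with increasing postpartum days".
- **Statistical analysis, main contrast:** before and after means are compared, and the mean difference is contrasted between arms with a 95% confidence interval and a p value. The stratified randomisation is accounted for, with no condition attached.
- **Statistical analysis, baseline check:** the arms are contrasted on variables that affect milk composition. Gestational age at delivery and time since delivery are named as examples. Then: "If differences are noted in baseline characteristics, inferences will be made based on observed and (linear regression) adjusted differences between groups".
- **Statistical analysis, other constituents:** fat, lactose, energy, calcium, phosphorus and sodium are handled in the same way as protein.
- **Randomization:** "Mothers of infants >3 but < 4 weeks postpartum will be randomized separately from those ≥ 4 weeks postpartum".
- **Breast milk composition:** in one cited study protein was "found to decrease significantly throughout the first four weeks of lactation (r = -0.45, p < 0.001"), and fell more slowly afterwards. In another, composition depended largely on postnatal age and only minimally on gestational age.

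**The concern.** The conditional sentence is a stated decision rule, not a detail held over for an analysis plan, and it is fixed badly in two ways.

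First, the data choose the analysis. In a randomised trial a baseline difference arises by chance. The reason to adjust for a covariate is that it predicts the outcome, and the article already describes postnatal age as the main determinant of changes in composition. Waiting for an imbalance to be noted adds nothing to that knowledge.

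Second, once the rule fires, two estimates carry the inference and neither is primary. If one confidence interval excludes zero and the other does not, the plan cannot say whether the trial showed an effect on protein. The results are meant to inform how preterm infants are fed, so that question needs one answer. The same ambiguity extends to the six other constituents.

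**Working it through.** **1. The plan's own figure.** Inputs from Sample size: "Sample size was calculated using a 2-sided test, an alpha error of 0.05 and a power of 80 percent"; "we designed the study to detect as significant a 20 percent or greater change in protein content"; "our study will recruit 44 participants, 22 assigned to the domperidone group and 22 to the placebo group". The standard deviation is not printed; the section refers to a cited publication. So 44 cannot be reproduced outright, but the coefficient of variation (CV) it implies can be found. With n per arm = 2(1.960 + 0.842)² CV² / 0.20²:

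- 22 per arm gives CV = 0.20 × √11 / 2.802 = 0.237.
- Forwards, CV 20% needs 16 per arm, 23% needs 21, 23.6% needs 22, 25% needs 25 and 30% needs 36.

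The figure of 44 is not shown to be wrong. The design effect is 0.20 / 0.237 = about 0.845 SD, which is used below.

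**2. Simulation of the two-result rule.** There were 20,000 trials per setting, with 22 per arm, balanced within two strata cut at 28 days. The observed model is arm + stratum. The adjusted model adds continuous postpartum days and gestational age. Assumptions not in the documents: entry days 21 to 56; the covariates explain 20% or 40% of outcome variance, split equally; the trigger is baseline p<0.05, baseline p<0.20, or always. The 20% is (−0.45)² = 0.2025, borrowed from the cited correlation.

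Type I error if either result may be claimed:

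| Trigger | 20% of variance | 40% of variance |
|---|---|---|
| Observed model alone | 5.0% | 5.1% |
| Adjusted model alone | 4.9% | 5.0% |
| Either, baseline p<0.05 | 5.1% | 5.2% |
| Either, baseline p<0.20 | 5.4% | 5.5% |
| Either, both always used | 6.9% | 7.7% |

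A separate simulation with blocks of four and the same 28-day cut gave about 5 to 5.6% under a triggered rule and about 6 to 7% if both are always used. Across both simulations the ranges are about 5 to 5.6% and about 6 to 8%.

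**3. How often the two results conflict**, at an effect of 0.845 SD:

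- Triggered at p<0.05: 0.0098 / 0.0504 = 19% of flagged trials (20% of variance) and 0.0127 / 0.0491 = 26% (40%).
- Both always reported: 9% and 12% of all trials.

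**4. Which covariate fires the trigger.** Because randomisation is stratified by postpartum duration, a p<0.05 flag on postpartum days occurs in only about 0.1 to 1% of null trials. In step 2 the rule fired in about 5% of trials, so most firings come from gestational age, which is not stratified.

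**5. Precision.** In step 2, power rises from 0.80 to 0.84 (20% of variance) and from 0.83 to 0.93 (40%), but half of the explained variance there is credited to gestational age. With postpartum days as the only covariate and the stratum already in the model, at an effect of 0.865 SD (80% power by the t test), always adding continuous days gains about 2 to 3 points if days explain 20% of variance, about 1 point at 10% and about 0 at 5%.

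**The case against.** The strongest reply is that postpartum time is already handled. A reader might infer from the conditional sentence that the allowance for decline promised under Primary outcome is made only when an imbalance is noted. The article does not support that. The stratum is itself postpartum duration, and the analysis accounts for it unconditionally. The natural decline over the 14 days also occurs in the concurrent placebo arm, so omitting continuous days does not bias the comparison. The promise is to consider the decline, not to regress on days. This part of the reply stands. What remains is that control is coarse: there is one cut at 4 weeks, and the upper stratum has no upper limit.

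It can also be said that the criterion for noting a difference and the covariate list belong in an analysis plan that is not shown, that the text says both results will be used rather than that one may be picked, and that group assignment stays blinded until the analysis is complete. The first two are fair, and the criticism does not depend on them. Blinding hides which arm is which. It does not hide whether each two-sided p value is below 0.05, and it does not settle which result decides. A later plan would have to overrule the published sentence, not merely fill it in.

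Finally, the cited correlation is for protein level in the first four weeks. These women enter at three weeks or later, when the decline slows, and the outcome is a before-after contrast. That limits any claim about precision, and the claim here is limited accordingly.

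**Conclusion.** The point holds for the conditional sentence: as written, each of the seven milk-content outcomes can have two conflicting answers, with no rule for choosing between them. Severity is minor to moderate.

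The cost in error rate is small if the trigger is a strict baseline test (about 5 to 5.6%) and larger if both results are always used (about 6 to 8%). These figures rest on assumed explained variance of 20 to 40%. The practical harm is the conflict itself, in roughly a fifth to a quarter of trials flagged at p<0.05 when the design effect is present. The precision lost by not always using continuous postpartum days is modest. Its exact size depends on the correlation of days with before-after change, which the documents do not give.

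Two stronger readings should not be drawn. One is serious inflation once imbalance is noted: ignoring the stratification, a covariate explaining 20% of variance and flagged at p<0.05 gives about 14% false rejections unadjusted and about 17% for either result. Stratification makes that event rare for postpartum days, and the article calls the influence of gestational age minimal. The other is a rise in power from 80% to 87-88%, which gives the stratum no credit.

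**What to change.** Replace the conditional sentence with one prespecified primary model for the before-after protein contrast, fitted whatever the baseline table shows. It should contain treatment arm, randomisation stratum and postpartum days at entry as a continuous variable. Gestational age at delivery is optional, given its minimal influence in the cited study. State that the treatment estimate from this model, with its 95% confidence interval and p value, is the sole primary inference. Report the other estimate as supportive only, and use the baseline table for description, not to choose the model. Apply the same wording to fat, lactose, energy, calcium, phosphorus and sodium.

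The cost is a change of wording and one or two degrees of freedom out of about 42 (44 women less two arm means). Both covariates are already planned for collection, and the sample size of 44 is unaffected.
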